# Abstract

## Background

This paper describes a randomised controlled trial (RCT) protocol aimed at investigating the efficacy of caregivers’ Mind-Mindedness training as an early intervention for preschoolers with social anxiety. Mind-mindedness, a caregiver's ability to recognise and respond to a child as an individual with their own thoughts, feelings, and intentions, is associated with secure attachment and socioemotional skills. While previous studies indicate brief Mind-Mindedness training may increase caregiver mentalisation in high-risk groups, there is a lack of rigorous evidence assessing its impact specifically on child social anxiety symptoms. Building on the well-established link between caregivers’ Mind-Mindedness and positive socioemotional outcomes in children, this study aims to bridge the existing research gap by directly testing the impact of Mind-Mindedness training on social anxiety.

## Methods

This randomised controlled trial aims to recruit 100 caregivers of preschool-aged 4 to 7-year-old children with social anxiety from the UK and Iran. The caregivers will be randomly assigned to either a mind-mindedness training group (n=50) or a peer support (control) group(n=50). The mind-mindedness training will involve three online sessions, each of one hour duration, focused on teaching strategies for using mind-minded comments with their children, across three consecutive weeks. The peer support (control) group will have access to a private online peer-support platform for sharing experiences. Measures of mind-mindedness, child social anxiety, attachment, and theory of mind will be assessed at baseline, post-intervention, and 3-month follow-up using established assessment tools.

## Discussion

The study aims to evaluate the effectiveness of a mind-mindedness parental intervention for social anxiety in children and to uncover the potential mediating roles of attachment and theory of mind in the relationship between mind-mindedness and child anxiety. The cross-cultural design, involving participants from the UK and Iran, will offer valuable information on the cultural aspect of the intervention. The training group is hypothesised to lead to increased mind-mindedness and reduced child social anxiety versus a peer support (control) group. This research can establish evidence for mind-mindedness training as an early intervention approach for childhood social anxiety, with implications for global mental health strategies targeting early caregiver-child relationships.

## Trial registration

Prospectively registered on ClinicalTrials.gov (ID: NCT06657014; registered on 23rd October 2024) and on the Iranian Registry of Clinical Trials (IRCT) Version 1 (ID: 80088; approved on 2nd November 2024). These registrations promote transparency and ensure compliance with international standards for reporting clinical trials.

# 1. Introduction

## 1.1 Background and Rationale

Social anxiety is a common mental health concern in early childhood and can impact a significant number of children, particularly preschoolers, and has long-term mental health implications if left unaddressed (1-3). Anxiety symptoms in young people have been exacerbated by the COVID-19 pandemic, highlighting the need for effective early interventions (4). Social anxiety is characterised by feelings of distress and avoidance of social settings due to a fear of negative evaluation (5) which can impair the development of social relationships and pose challenges in adapting to school life (6, 7). Anxiety levels often begin to present between the ages of 2-4, likely due to significant life changes such as starting preschool (8, 9).

[figure not shown]

It is also essential to understand that certain expressions of anxiety, such as separation anxiety, are considered typical during early childhood and often indicate normal developmental transitions, and are developmentally normative during this period. These symptoms frequently arise in response to significant milestones, including starting preschool, navigating new peer relationships, and experiencing temporary separations from caregivers (10, 11). It is crucial to distinguish between developmentally appropriate anxiety and clinically significant anxiety symptoms for early identification and intervention.

The preschool period is a critical stage in a child's life, as it involves significant changes for the child, with changes to the teacher, peers, and environment. These changes can be challenging to navigate (12-14). Parenting style and attachment are strongly linked to childhood anxiety (11, 15). Early intervention for preschoolers with social anxiety, through targeted approaches that focus on parenting and attachment, addressing caregiver behaviours as a key mechanism of influence, can help prevent symptoms from escalating into more severe disorders as the child develops (16, 17). The preschool years are, therefore, of critical importance for anxiety prevention efforts. While the impact of parenting style and attachment on a child's anxiety is well-documented, interventions often focus exclusively on the child, neglecting the crucial role of caregiver behaviour (15).

One particular aspect of caregiver behaviour is Mind-Mindedness (MM). MM involves a caregiver's ability to recognise and respond to a child as an individual with their own thoughts, feelings, and intentions (18, 19). Higher levels of MM are associated with secure attachment and positive socioemotional outcomes (18, 20-22). However, the direct impact of caregiver MM on child social anxiety remains underexplored. While the concept of MM is well-established in developmental psychology, its direct impact on child social anxiety has not been extensively explored in empirical research. Nevertheless, an increasing body of evidence indicates that MM has a causal influence on critical developmental mechanisms, particularly attachment (18, 19) and Theory of Mind (ToM) (20, 21, 23, 24) that are subsequently linked to anxiety outcomes.

MM is not just a descriptive ability; it represents a dynamic, relational process in which caregivers actively interpret and respond to their child's internal states. Parents who exhibit higher levels of mind-mindedness by making appropriate and attuned comments about their child's thoughts, emotions, and intentions have been shown to promote better emotional regulation, social competence, and executive functioning in their children (Meins, 1999; Bernier et al., 2010). These positive outcomes are likely shaped by more secure attachment relationships and enhanced ToM development, both of which act as protective factors for social anxiety (19, 20, 24).

Although MM has yet to be directly tested as an intervention for social anxiety, its known effects on attachment and ToM make it a promising candidate for early intervention. This study seeks to rigorously examine the efficacy of MM training for caregivers in reducing symptoms of social anxiety in children by reinforcing these foundational developmental processes.

Meins presents a link between lower MM and a child’s insecure attachment (25-27). Several interventions have been developed to enhance maternal MM, including video feedback and smartphone apps, all of which have demonstrated promise across diverse caregiver populations (28-30). Importantly, it appears that caregivers' socioeconomic status and child characteristics do not significantly impact MM levels, indicating that these interventions can be broadly applicable regardless of background or individual child traits (25, 31). A relationship has been shown between maternal and paternal MM with child attachment security and theory of mind abilities (23, 24).

Based on attachment theory, early experiences with caregivers shape internal working models that affect future relationships (11). Thus, children who are securely attached are better able to understand different perspectives within relationships (32). Insecure attachment is a risk factor for internalising problems such as anxiety (33, 34) while secure attachment is associated with appropriate mind-related comments and fewer non-attuned comments (26, 35). Previous studies have indicated that parent cognitions may play a vital role in mediating the relationship between parent and child difficulties (22, 36-38). Some research suggests that MM might be a better predictor than the sensitivity of attachment status (39), at least be a prerequisite for sensitivity (40). Therefore, focusing on MM in interventions may improve outcomes for families.

Maternal MM has been found to be predictive of children’s ToM, the ability to understand and attribute mental states to oneself and others (41-43). Mothers who describe their children in more mental terms have children who perform better on tasks that require an understanding of false beliefs (27, 44). Moreover, higher ToM abilities are linked to secure attachment in preschoolers (45, 46). On the other hand, poor ToM abilities are associated with childhood anxiety disorders and negative interpretive biases (47, 48).

This study will focus on examining whether training caregivers in MM can reduce social anxiety in preschoolers by improving attachment security and ToM abilities. Understanding these pathways from MM to childhood anxiety can help inform preventative interventions targeting early socio-cognitive development. Therefore, the proposed mechanisms in this study are attachment and the theory of mind. MM strongly predicts child attachment security (40), which provides an anxiety buffer. Insecure attachment is linked to increased internalising symptoms (34). Caregiver’s MM also forecasts children’s theory of mind abilities (49).

Parental mentalization (MM) is strongly linked to secure attachment in children. Interventions that target MM could improve attachment security. Future research should prioritise MM as a key intervention target to address gaps in how attachment behaviours are passed from parent to child, especially when parents struggle to understand and respond to their child's emotional needs. Consistent parental behaviours, such as emotional responsiveness, promote secure attachment in children. Interventions, such as training programmes to enhance parents' ability to perceive and interpret their child's emotions, can help bridge these gaps, supporting children's emotional and social development (23, 35, 50, 51).

Various interventions have been developed to enhance MM, ranging from video feedback to smartphone apps, demonstrating promise in diverse caregiver populations (28-30). Upon closer examination of these interventions, it becomes evident that their effectiveness largely depends on addressing the unique needs of caregivers. Factors such as accessibility, ease of use, and the relevance of the content play crucial roles in determining the success of each intervention format. By enhancing caregivers’ MM, they are better equipped to cultivate secure attachments and establish a nurturing environment, and they can significantly decrease the symptoms of social anxiety in their children.

Various interventions have been conducted by researchers to explore the link between child development and caregivers' mind-related comments. Schacht et al.(2017) reported that a single-session video-feedback intervention was effective in reducing non-attuned comments (30). This intervention proved to be beneficial for mother-infant interactions even up to the second year of life. Another study conducted by Larkin et al. developed the BabyMind app, which was successful in increasing MM among adolescent mothers (29). Walker's (2012) research emphasised the importance of MM in preschool clinical interventions (52).

This paper proposes an RCT of MM training for caregivers of socially anxious preschoolers. This study emphasises the need to adapt interventions for diverse populations. Research indicates culture shapes caregiving approaches, parenting behaviours, and attachment styles (53, 54). Some studies reveal differences in MM across Western and Eastern cultures. For instance, British parents exhibit higher MM towards children compared to Chinese parents, but both show positive links between MM and child theory of mind (55). Research indicates that Western mothers engage in more mental state talk with children than Eastern mothers (56). Collectivist values in Eastern cultures prioritise hierarchy and conformity versus individuality in the West impacts manifestations of MM in parent-child interactions (57, 58). According to some research, traditional gender norms can also affect father-daughter relationships and emotional attunement in Persian families specifically (59, 60). For instance, in a study comparing parenting practices in the UK and India, they found notable differences: UK mothers made more mind-minded comments, while Indian mothers issued more instructions and positive comments, reflecting cultural priorities (61). These differences highlight the influence of cultural contexts on parenting practices. Recognising and understanding these variations can guide the development of interventions sensitive to cultural contexts, ultimately promoting healthier outcomes for children worldwide(53, 62).

# 2. Materials and Methods

## 2.1 Objectives

The main aim of this study is to evaluate the efficacy of the caregiver's MM training in reducing social anxiety symptoms among preschool children. Additionally, to examine how culture (Iranian and British) moderates the relationship between caregivers’ MM training and reductions in social anxiety symptoms among preschool children.

## 2.2 Trial design

This study protocol outlines the design and methodology of a randomised controlled trial aimed at investigating whether MM training for caregivers can effectively reduce social anxiety symptoms in preschoolers by employing a cross-cultural approach involving caregivers from the UK and Iran. Participants will be randomly assigned to either the MM training intervention group or a peer support (control) group. Randomisation will be carried out separately for each country's sample. Stratified random sampling will ensure a balanced allocation within each country's participants.

## 2.3 Study setting

The study will be conducted in two countries: the United Kingdom and Iran. The intervention and all measurements will be held online.

## 2.4 Participants

The study aims to recruit 100 primary caregivers (aged 18-60 years) of preschool-aged children (aged 4-7 years) who exhibit symptoms of social anxiety. Eligible participants must reside in either the United Kingdom or Iran. Caregivers whose children have existing clinical diagnoses or are currently receiving other forms of treatment or support will not be included in the study. Children will be included in the study based on symptoms of social anxiety reported by caregivers, assessed using the Spence Children’s Anxiety Scale – Parent Version (SCAS-P). Although the SCAS was initially validated for children aged 6 to 12 (63),it has been reliably utilised with younger children aged 4 to 6 in parent-report studies (Edwards et al., 2010). For this study, the inclusion criteria will specifically focus on elevated scores in the social phobia subscale. Those whose anxiety profiles indicate separation anxiety or general behavioural inhibition, rather than social anxiety, will be excluded during the screening process. Children with a confirmed clinical diagnosis, such as autism spectrum disorder, generalised anxiety disorder, or ADHD, along with those currently receiving psychological or educational treatment, will not be eligible for participation. The research team will not make any formal diagnoses; inclusion decisions will be based solely on parent-reported data obtained through the SCAS-P. This approach guarantees consistency across participants while focusing on observable symptoms rather than clinical labels.

Participants will be recruited through a combination of targeted outreach and community engagement strategies. This includes advertisements in preschools and nurseries, referrals from early years professionals, and word-of-mouth recommendations from other caregivers. The recruitment strategy is designed to ensure a demographically diverse yet diagnostically homogeneous sample of families, with equal representation from the UK and Iran.

Due to the nature of the intervention, participant blinding is not possible, as caregivers will be fully informed of their group allocation, either participating in mind-mindedness training sessions or joining a peer-support group. However, the assessors responsible for data collection and analysis, including those evaluating mind-mindedness, child social anxiety, attachment, and theory of mind, will remain blinded to the group allocations to ensure an unbiased evaluation of outcomes.

To enhance participant retention and reduce attrition, several strategies will be implemented. These will include clear communication protocols, flexible scheduling options, and modest incentives for completing assessments. Participants will receive systematic reminders about their sessions, and a dedicated support structure will be available throughout the duration of the study. Additionally, data from participants who deviate from the protocol will be included in the intention-to-treat analysis. This approach will help preserve the integrity of the randomisation process while minimising bias and ensuring that the findings are practically applicable and generalizable.

| Inclusion Criteria | - Primary caregiver of a child aged 4-7 years  - Caregiver aged 18-60 years  - Living in the UK or Iran  - Observable social anxiety symptoms in children confirmed by a screening tool |
| --- | --- |
| Exclusion Criteria | - Child with another clinical diagnosis  - Child receiving other support/treatment |

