## 2.5 Procedure

Participant allocation will be carried out using a computer-generated randomisation sequence through Random Allocation Software 2.0, which will assign caregivers to either the mind-mindedness (MM) training intervention group (n=50) or the peer support control group (n=50). The randomisation will be stratified by country (UK and Iran) to maintain a balanced allocation within each cultural context (FIGURE

1).

Data collection will take place at three time points: baseline (T0), post-intervention (T1), and 3-month follow-up (T2). At each time point, data will be collected through validated caregiver-report measures (FIGURE

2). Mind-mindedness will be assessed using the Mind-Mindedness Coding Manual 2.2 (64), which offers a structured framework for coding caregivers' descriptions of their children. This method evaluates both the frequency and appropriateness of the mental-state language caregivers use when describing their child. It has been widely applied in developmental studies involving preschool-aged children. Child social anxiety symptoms will be measured using the Spence Children’s Anxiety Scale – Parent Version (SCAS-P)(65), while the scale was initially validated for children aged 6 to 12, it has also been effectively used in parent-report studies with younger children aged 4 to 6(66). Attachment security will be assessed using the Attachment Insecurity Screening Inventory (AISI) for Preschoolers (67). This caregiver-report tool is specifically designed for two age groups: children aged 2 to 5 years and 6 to 12 years old, which evaluates both anxious and avoidant attachment patterns. The AISI has demonstrated good construct validity and cross-cultural applicability, making it suitable for use in both the UK and Iranian populations.

The assessment of Theory of Mind (ToM) will be conducted using the Theory of Mind Task Battery (68) for evaluating the theory of mind. The battery has been validated for use with preschool children and demonstrates strong convergent validity with other socio-cognitive measures. All measures were selected based on their age appropriateness, prior validation within preschool populations, and their cross-cultural applicability.

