## 2.6 Intervention

This study aims to reduce social anxiety in preschoolers by tailoring an MM intervention that targets parents to alleviate social anxiety levels in their children. Collaborating with parents and caregivers will result in a more effective and tailored solution that resonates with their practical needs and experiences. Their input can lead to a more feasible and impactful study design, refining eligibility criteria, recruitment, and data collection procedures. A participatory co-design was conducted in order to strengthen the quality and outcomes of this research. The intervention will be identical in both countries, with the only difference being the language used for the programme. All other elements, such as the structure, content, delivery methods, and materials of the MM training programme, will remain uniform across both locations.

The MM training programme will consist of three online sessions, each lasting one hour and conducted over three consecutive weeks. The training sessions will be conducted through Zoom, and participants will receive a unique link to access the platform securely. This training is designed to equip caregivers with strategies for attuned, mentalizing caregiving, focusing on enhancing their ability to understand and respond to their child's emotional and mental states.

The first session will introduce the concept of mind-mindedness and its importance in caregiving. It will include psychoeducation on the development of social anxiety in children and how caregiver responsiveness plays a crucial role. Caregivers will also be introduced to basic emotion coaching techniques, which will be explored in more depth in the second session. The second session will focus on teaching and practising these emotion coaching techniques, helping caregivers recognise, validate, and guide their children's emotions in a supportive manner. The final session will deepen the caregivers' understanding through reflective discussions and advanced role-play scenarios that address common challenges in caregiving with socially anxious children.

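### Child social anxiety and attachment are rated by caregivers who know their allocation, so blinding staff cannot secure the unbiased evaluation the protocol promises

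*Protocol*

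**What the plan says.** Protocol section 2.4 (Participants) is open about the caregivers: "participant blinding is not possible, as caregivers will be fully informed of their group allocation". The next sentence sets staff blinding against this. It concerns the assessors who collect and analyse the data, "including those evaluating mind-mindedness, child social anxiety, attachment, and theory of mind", and says they "will remain blinded to the group allocations to ensure an unbiased evaluation of outcomes".

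Section 2.5 (Procedure) states who supplies the data: "At each time point, data will be collected through validated caregiver-report measures". For the main outcome it says: "Child social anxiety symptoms will be measured using the Spence Children’s Anxiety Scale – Parent Version". It describes the AISI, used for attachment, as an instrument that caregivers complete. Mind-mindedness is coded from caregivers' descriptions of the child, and theory of mind is assessed with a task battery.

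On what the two arms are told, section 2.6 says of the first training session: "It will include psychoeducation on the development of social anxiety in children and how caregiver responsiveness plays a crucial role". Section 2.7 says that controls use an online forum and receive neither structured training nor psychoeducation, and it calls this an active control condition.

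**The concern.** On a parent-report scale the person who judges the child's symptoms is the parent. Staff who send out, score or analyse the form make no judgement that blinding could protect. Section 2.4 nonetheless offers staff blinding as the safeguard and lists social anxiety and attachment among the outcomes it covers.

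Reducing child social anxiety is the main aim (section 2.1), and SCAS-P at T1 enters the primary between-arm regression (section 2.8.2). The training also sets out to change how caregivers perceive and interpret their child. A caregiver's rating could therefore move because of expectation or altered perception while the child's anxiety stays the same. As the protocol is worded, such a result would be reported as coming from an unbiased evaluation.

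**Working it through.** The point is mainly textual, and the protocol gives no figure to reproduce. Taking the outcomes in turn:

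| Outcome | Who makes the judgement | Can it be blind to arm? |
|---|---|---|
| Social anxiety (SCAS-P) | Caregiver, section 2.5 | No; the caregiver knows the arm, section 2.4 |
| Attachment (AISI) | Caregiver, section 2.5 | No, for the same reason |
| Mind-mindedness | Coder, working from caregivers' descriptions, section 2.5 | The coding can be; the descriptions come from unblinded caregivers |
| Theory of Mind Task Battery | Not stated | Only if a blinded assessor administers or scores it |

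No teacher, clinician or observer rating of anxiety or attachment is described. The primary model adjusts for the baseline score, but that cannot remove a shift in reporting that arises after allocation.

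**Illustration of size.** Inputs:
- 89 completers, the minimum sample size in section 2.8.1, in two equal arms.
- Two-sided 5% test (section 2.8.4), normal approximation.
- No true effect.
- A differential reporting shift b of 0.1, 0.2 or 0.3 residual SD. This is an assumption; the protocol gives no value.

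Standard error of the arm difference: 2/√89 = 0.212 residual SD.

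Chance of a significant result: P(|Z + b/SE| > 1.96).

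- b = 0.1: b/SE = 0.472. Tails 0.068 + 0.008, about 7.6%.
- b = 0.2: b/SE = 0.943. Tails 0.155 + 0.002, about 16%.
- b = 0.3: b/SE = 1.415. Tails 0.293 + less than 0.001, about 29%.

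The answer changes little with the number of completers. With 50 per arm (SE = √(2/50) = 0.200) the three values are 7.9%, 17.0% and 32.3%. With 43 per arm, roughly 15% attrition, they are 7.5%, 15.3% and 28.5%.

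**The case against.** The strongest reply is that the protocol hides nothing. It states that caregivers cannot be blinded directly before the blinding sentence, and that sentence is about staff who collect and analyse data. Read that way, the statement that staff are blinded may be true, and it is ordinary practice. This much stands: a reader might infer that the protocol claims the SCAS-P or AISI rater is blinded, and it does not say so. What does not stand is the purpose clause. Even if every staff member is blind, the evaluation of these two outcomes is not thereby unbiased, and the protocol nowhere links the caregivers' knowledge of their arm to the outcomes they rate.

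A second reply is that the control is active. Peer support, including the sharing of coping strategies, may narrow the difference in expectation between arms. It does not blind the rater, and the psychoeducation still differs by arm.

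A third is that the percentages rest on an assumed shift and describe the cost of unblinded parent report, not the cost of one sentence. That is correct, and they are used here only as illustration.

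Two further inferences are tempting but unsupported. One is that section 2.5 makes every outcome caregiver-report. Its general sentence is loose, and the same section goes on to describe coded descriptions and a task battery. The other is that theory of mind could serve as blinded corroboration of a fall in anxiety. The protocol does not say who administers the battery. Section 2.8.2 already lists theory of mind among the primary-analysis outcomes, and section 2.8.3 treats it as a mediator. A change in it would not show that anxiety fell.

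**Conclusion.** The concern holds in a limited form. The assurance in section 2.4 is wrong for SCAS-P and AISI, because the caregiver makes both ratings and knows the allocation. Nothing elsewhere in the protocol repairs this. It matters most for SCAS-P, on which the main aim depends.

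This rests on the protocol's own description of the measures and on no numerical assumption. The size of any bias is unknown. Under assumed shifts of 0.1 to 0.3 residual SD, the false-positive rate at 89 completers would run from about 7.6% to 29%. A reader might infer that the SCAS-P result will be biased by such an amount, or that parent report is an unacceptable design. The documents support neither. Unblinded parent report is a legitimate choice; the fault is in presenting it as protected by assessor blinding.

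**What to change.** In section 2.4, state blinding outcome by outcome:

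- Describe SCAS-P and AISI as unblinded caregiver reports.
- Limit the blinding statement to mind-mindedness coding, scoring and analysis. Extend it to the Theory of Mind Task Battery only if the sponsor confirms that a blinded assessor administers or scores it.
- Remove the assurance of unbiased evaluation for SCAS-P and AISI.
- Word the main conclusion as an effect on caregiver-reported social anxiety, and name unblinded reporting as a limitation.

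These are text changes using the existing measures, plus one confirmation from the sponsor about the task battery. The cost is a more modest claim. The change tells readers about the risk shown above but leaves its size as it is.
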